### Data collection

For the duration of the study, migrant patients will be assigned to a personal clinician as they will be required to complete questionnaires about each other. Before the start of treatment, clinicians will be informed of the randomization group to which the migrant patient has been assigned. Participating confidants will have one consultation with the personal clinician of the patient that they represent, according to the patient’s randomization status.

The principal investigator will receive notification regarding the date of the initial treatment session to schedule an appointment for the migrant patient to take the first-stage survey on perceived empathy, either face-to-face or online. The respective questionnaires must be completed within one week of the first session, and interpreters will be employed as necessary. The patient proceeds with subsequent treatment following the treatment plan. The procedure for participating confidants will be identical, and their involvement will cease upon finishing the perceived empathy questionnaire (see **Figure 1**).

In the intervention group, treatment sessions will proceed using CFI questions. The control group will receive standard care in which CFI questions are avoided. After each initial treatment session, clinicians will complete a brief online questionnaire to evaluate their fidelity to the CFI. Fidelity is expected for migrant patients who were randomized in the intervention group, and infidelity to the CFI is expected in the control group. In addition, the clinicians will be asked to respond to empathy-related questions.

The principal investigator will receive notice of the migrant patient’s fifth treatment session appointment with their personal clinician to schedule the second-stage questionnaire completion. The patients will have an in-person or online appointment where they will answer the same questions about perceived empathy, in addition to supplementary questions about the therapeutic working alliance. The questionnaires need to be completed within one week of the fifth session. After the completion of these questionnaires, the patient’s participation concludes. Subsequently, clinicians will conduct an online questionnaire after every fifth treatment session. This questionnaire includes the same fidelity check and empathy questions as offered after the first treatment session and additional questions regarding the therapeutic working alliance. Clinicians will continue treating other study participants and are required to reiterate the aforementioned protocol for each participating patient under their care. Their participation in this study will end after completing the questionnaires of their final migrant patient.

### Benefits and consequences of participation

In line with the aim of this study, patients in the intervention group may benefit from the experience of a stronger therapeutic working alliance and a higher level of perceived cultural empathy. The risk of negative consequences of participation is estimated to be as low, if not non-existent since patients in the control group also receive the current standard of treatment and care. The additional burden of participation for patients is to complete questionnaires before and after the first and after the fifth treatment session, which will take some extra time.

Participating clinicians benefit from free CFI training that can enhance their clinical competencies and future therapeutic working alliances with patients and their confidants. The additional obligation for participating clinicians entails investing additional time in consultations with confidants and completing the online surveys for each of their participating patients before and during the study, which adds extra time to their workloads.

### Sample size

The power analysis indicated that at least 164 patients would need to be included in this study to obtain results indicating a practically relevant improvement in the therapeutic working alliance. The standard deviation (SD) used is based on previous research on the psychometric properties of the Working Alliance Inventory (WAI-12). The power analysis was performed in G*Power version 3.1.9 (27) for the comparison of two independent groups (t-test) with a power of (1-ß) = .80, a significance level <.05, a minimum clinically relevant difference of half a SD = .39, and an allocation ratio of 1. This number of patients is required based on the more realistic result of half, rather than a full SD. For more in-depth and precise analyses using a linear regression analysis, including the interaction variables, 209 patients will be needed. Initially, the investigators aim to enroll 164 patients.

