To address miscommunication in diagnosis and treatment, initiatives have been taken to include cultural identity, idioms of distress, support systems, and clinician-patient relationships in interviews (1, 8). In 2013, the Cultural Formulation Interview (CFI) was included in the fifth edition of the Diagnostic and Statistical Manual of Mental Disorders (DSM-5) (9). This semi-structured interview incorporates the migrant patient’s social and cultural context and addresses beliefs, customs, and identity in the diagnostic and treatment process. The interview aims to increase mutual understanding and rapport between patients and clinicians based on an interest in and a better understanding of the cultural background of these patients to prevent cultural misunderstandings (10). The CFI was found to be a feasible, acceptable, and useful instrument in mental healthcare and it is used increasingly among different populations worldwide (11–13). In general, therapeutic working alliances benefit from the use of the CFI (7, 14). However, CFI use can also negatively affect communication and the therapeutic working alliance between migrant patients and clinicians when questions about culture may upset the patients and jeopardize the quality of the alliance (7, 15, 16). To avoid the latter scenario, it is recommended to train clinicians in the use of the CFI, provide supervision, and focus on compliance and fidelity in administering the interviews (7). It is still unclear whether this strategy creates stronger therapeutic working alliances, which may contribute to reducing high dropout rates, improving treatment outcomes, and enhancing the quality of mental health care (7).

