It is hypothesized that this study will show that implementation of the CFI may have a positive, strengthening effect on the therapeutic working alliance between migrant patients and clinicians moderated by (perceived) cultural empathy. Therefore, the central research question of this study is: Does the use of the CFI influence the therapeutic working alliance between migrant patients and clinicians? In addition, it will be examined whether perceived cultural empathy moderates (changes strength and direction) or mediates (explains) the effect of CFI use on the therapeutic working alliance.

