The first limitation to consider regarding this multicenter RCT is its complexity. Many different parties are involved, especially during recruitment and data collection, which must be carefully managed and monitored throughout the process. Any ambiguity in roles can delay progress, complicate enrollment, and possibly lead to participant withdrawal. In addition, the variety of languages spoken by patients can cause problems in explaining the study, answering questions, and completing the questionnaires. In an attempt to overcome language barriers, precautions were taken by providing information letters in several different languages, using validated translations of the questionnaires, and using licensed interpreters when and where needed. Another limitation may be the large sample size needed to obtain reliable results while participants are free to stop participating and may drop out for many reasons. This aspect may compromise the power of this study. To reduce this risk, rather than stopping for this reason, and to be able to include sufficient migrant patients, more mental health centers could be included. Finally, the CFI training given to all participating clinicians and any prior experience of clinicians working with the CFI before participation may influence and prime the content of the conversations in the control group, despite efforts to avoid using CFI questions in the control group. The decision to conduct this study pragmatically may therefore lead to contamination and underestimation of the results.

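### The stated basis for 164 patients (half an SD, 80% power, alpha .05, 1:1) gives 128 two-sided or 102 one-sided; 164 is what a standardised effect of .39 tested one-sided gives

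*Protocol article*

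**What the plan says.** The Sample size section of the protocol article gives the result of the calculation and most of its inputs.

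- Result: "The power analysis indicated that at least 164 patients would need to be included in this study".
- Test: a G*Power calculation "for the comparison of two independent groups (t-test"), "with a power of (1-ß) = .80" and a significance level written as below .05.
- Effect and ratio: "a minimum clinically relevant difference of half a SD = .39, and an allocation ratio of 1".
- The section then repeats that the number rests on half an SD and not a full one, and sets 164 as the initial enrolment aim.

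The SD is attributed to earlier psychometric work on the WAI-12, but its value is not printed. Sidedness is not stated there, and the Data analysis section says only that mean WAI scores will be compared by t-test.

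On direction, the Introduction hypothesises a strengthening effect, and the Sample size section speaks of an improvement. The central research question, however, is neutral: "Does the use of the CFI influence the therapeutic working alliance between migrant patients and clinicians". The Introduction also reports possible harm: "However, CFI use can also negatively affect communication and the therapeutic working alliance between migrant patients and clinicians".

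**The concern.** The section prints its inputs and its output, so the two can be compared, and they disagree. An effect defined as half an SD is d = 0.50 by construction. The number .39 can then only be the same difference in raw WAI units. If .39 is instead the standardised effect, calling it half an SD is false. Neither reading makes the sentence agree with 164.

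At stake is what the trial can claim about its own sensitivity. A reader who takes the section at its word will believe that 164 patients give 80% power for half an SD. The power that 164 actually gives depends on an effect size that the text describes in two incompatible ways and on a sidedness that it does not give.

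**Working it through.** **Inputs** (protocol article, Sample size): total 164, so 82 per arm; power .80; alpha .05; ratio 1; difference equal to half an SD and equal to .39.

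**Implied SD and effect.** SD = .39 / 0.5 = 0.78. d = .39 / 0.78 = 0.50.

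**Method.** Exact power for a two-sample t-test with n per arm: df = 2n − 2, noncentrality = d × √(n/2), critical value t(1 − α) one-sided or t(1 − α/2) two-sided. Solve for the smallest n with power of at least .80.

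**Step 1: try to reproduce 164.**

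| d | Sidedness | n per arm | Total | Noncentrality | Power at that n |
|---|---|---|---|---|---|
| 0.50 | two-sided | 64 | 128 | 0.50 × √32 = 2.83 | .8015 |
| 0.50 | one-sided | 51 | 102 | 0.50 × √25.5 = 2.52 | .806 |
| 0.39 | two-sided | 105 | 210 | 0.39 × √52.5 = 2.83 | at least .80 |
| 0.39 | one-sided | 82 | **164** | 0.39 × √41 = 2.50 | .8001 |

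In the last row, 81 per arm gives .796, so 82 is the smallest n that qualifies.

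**Step 2: cross-check by the normal approximation**, n per arm = 2(z_α + z_β)² / d², rounded up.

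- d = 0.39, one-sided: 2 × (1.645 + 0.842)² / 0.1521 = 81.3, so 82 per arm and 164 in total.
- d = 0.39, two-sided: 2 × (1.960 + 0.842)² / 0.1521 = 103.2, so 104 per arm and 208.
- d = 0.50, two-sided: 2 × (1.960 + 0.842)² / 0.25 = 62.8, so 63 per arm and 126.
- d = 0.50, one-sided: 2 × (1.645 + 0.842)² / 0.25 = 49.5, so 50 per arm and 100.

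**Step 3: what 164 analysed patients deliver** (82 per arm, alpha .05, independent patients, complete data).

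| True d | Two-sided power | One-sided power |
|---|---|---|
| 0.50 | .889 | .939 |
| 0.39 | .699 | .800 |

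The effect detectable two-sided with 80% power is d = 0.44.

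**Step 4: other routes to 164.** With d = 0.50 and 80% power, 164 also results from a two-sided alpha of .02 or a one-sided alpha of .01. Inflating 128 for about 22% loss comes to the same place: 128 / 0.78 = 164.1. The article states none of these and presents 164 as the direct output of the power analysis.

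The 209 patients quoted for the regression with interactions are a separate figure without printed inputs. They are not tested here.

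**The case against.** The strongest defence is that 164 does no harm. The section says twice that the target is half an SD, and for that target 164 is larger than needed under either sidedness. This stands. A reader might infer from the mismatch that the trial is underpowered, but the document does not support that. The 70% figure requires setting aside the explicit half-SD wording and also testing two-sided.

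A second defence concerns cause. A reader might conclude that .39 was certainly typed in as Cohen's d with a one-sided test. The exact match is persuasive, but it remains an inference: the SD and sidedness are not printed, the psychometric source is not at hand, and step 4 shows that unstated inputs could reach 164 as well. What is established is narrower: 164 does not follow from the inputs as printed.

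Third, a one-sided test might seem to contradict the document outright. It does not. The stated hypothesis is directional and the sizing is for an improvement, which supports one-sided testing. The neutral question and the acknowledged possibility of harm point the other way, and the remark on harm is literature background, not a test specification. Sidedness of the final test may also be fixed in a fuller document. Even if one-sided testing is granted, half an SD needs 102, so the discrepancy remains.

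Finally, one might present the 36 patients between 128 and 164 (36 / 164 = 22%) as a built-in dropout allowance. The article says of dropout that "This aspect may compromise the power of this study", and answers with possible extra centres and multiple imputation; it never derives 164 from a loss rate. The margin also assumes independent patients. The Data collection section has clinicians treating several participants, and the Data analysis section says that the data structure will be taken into account. A design effect of 164 / 128 = 1.28 would use up the whole margin before any dropout.

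**Conclusion.** The point holds as an error in the stated justification. On the printed basis the requirement is 128 patients two-sided or 102 one-sided, so 164 exceeds it by 36 or 62. The figure equals the one-sided requirement for a standardised effect of .39, which is consistent with a raw difference having been used as Cohen's d.

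For half an SD, 164 gives about 89% power two-sided. If d = 0.39 was the real target and the test is two-sided, it gives about 70%, and 210 would be needed for 80%. All these figures assume a t-test at alpha .05, equal arms, independent patients and a complete fifth-session WAI. No loss of power is shown for the target that the article names. What is shown is that the stated effect, power and number do not belong together.

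**What to change.** State the SD, the standardised effect and the sidedness in the Sample size section, rerun the calculation, and delete the claim that 164 is required for half an SD. Then, according to what was intended:

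- **Half an SD, two-sided:** difference 0.39 WAI points, SD 0.78, d = 0.50, two-sided alpha .05. 128 analysed patients are needed, and 164 gives about 89% power assuming independent patients and complete data.
- **Half an SD, one-sided:** say so and justify it against the neutral research question and the reported possibility of harm. 102 analysed patients are needed, and 164 gives about 94% power under the same assumptions.
- **d = 0.39:** remove the half-SD wording, and report that 164 gives about 70% power two-sided, with 210 needed for 80%.

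Do not describe the gap between 128 and 164 as a guaranteed 22% attrition allowance, since clustering by clinician or centre would draw on the same margin.

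The cost is a rerun of the calculation and a few sentences. The enrolment target of 164 need not change.

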**Results:**

This study will indicate whether or not the CFI strengthens the therapeutic working alliance between patients and clinicians, as moderated and/or mediated by perceived empathy.

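### The plan states a need for 209 patients for the regression with interactions but initially aims for 164, gives no rule for reaching 209, and still promises a moderation answer

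*Protocol article*

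**What the plan says.** The Sample size section of the protocol article gives a minimum of 164 patients. This comes from a two-group t-test at 80% power and the 5% level, with equal arms. The difference to be detected is put as "a minimum clinically relevant difference of half a SD = .39". For the regression, the section says "For more in-depth and precise analyses using a linear regression analysis, including the interaction variables, 209 patients will be needed". The section closes with the recruitment aim: "Initially, the investigators aim to enroll 164 patients".

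No effect size, sidedness or number of tested terms accompanies 209, and no condition is given for moving from 164 to 209.

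The Data analysis section plans a regression to test whether empathy, measured by the BLRI and the SEE, moderates the effect of the CFI on the working alliance. Moderation is also part of the hypothesis at the end of the Introduction. The Results paragraph of the abstract says: "This study will indicate whether or not the CFI strengthens the therapeutic working alliance between patients and clinicians, as moderated and/or mediated by perceived empathy".

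**The concern.** The plan names a size for its interaction analyses, sets its target below that size, and says in the abstract that the study will answer the moderation question. A shortfall in power matters most when the interaction is not significant. That result would be weak evidence either way, but under the abstract's wording it could be reported as an answer.

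There is a second question about 209 itself. Interactions are often smaller than main effects and need more patients. If 209 rests on the effect size used for the main comparison, it covers only a large interaction.

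**Working it through.** **Inputs.** From the Sample size section: alpha 0.05, power 0.80, difference 0.39, allocation 1:1, sizes 164 and 209. Sidedness is not stated for either size. I treat 0.39 as a standardised difference d, because that reproduces 164. A d of 0.50 (half an SD taken literally) gives 102 one-sided or 128 two-sided, which is neither stated figure.

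**Gap on the face of the text.** 209 − 164 = 45, and 45/209 = 22%.

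**Reproducing 164.** A two-sample t-test at d = 0.39 with power 0.80 gives N = 164 one-sided (power 0.8001) and N = 210 two-sided.

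**Reproducing 209.** For one coefficient in a linear regression, f² = d²/4 = 0.39²/4 = 0.0380. The 1-df noncentral F test at alpha 0.05 and power 0.80 gives N = 209. The answer is the same for 1, 2, 3, 4, 5, 10 and 15 predictors in all.

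**What f² = 0.038 means for an interaction.** Take arm coded 0/1 at 1:1, a standardised moderator and residual SD 1. An interaction coefficient b then has f² = b²/4. So f² = 0.038 means b = 0.39: the CFI effect changes by 0.39 SD for each SD of empathy, as large as the planned main effect. Setting the residual SD equal to the total SD assumes that the model explains little other WAI variance.

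**Power, two-sided.** The normal approximation is Φ(√(f²N) − 1.960). The noncentral F value (3 predictors) follows in the last column.

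| Interaction per SD of empathy | N | √(f²N) | Normal | Noncentral F |
|---|---|---|---|---|
| 0.39 (f² = 0.0380) | 164 | 2.497 | 0.704 | 0.699 |
| 0.39 | 209 | 2.819 | 0.805 | 0.801 |
| 0.195 (f² = 0.0095) | 164 | 1.249 | 0.238 | 0.237 |
| 0.195 | 209 | 1.410 | 0.291 | 0.289 |

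The interaction of 0.195 would need 4 × ((1.960 + 0.842)/0.195)² ≈ 826 patients for 80% power.

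**Both empathy scales.** Testing the BLRI and SEE interactions jointly (2 df, 5 predictors) at a combined f² of 0.038 needs 257.

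**Sensitivity to residual variance.** If the model explains a share R² of WAI variance, f² becomes f²/(1 − R²). The documents give no R², so 20%, 30% and 50% are assumptions. Power at 164 is then:

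| R² | 0.39 per SD | 0.195 per SD |
|---|---|---|
| 0 | 0.70 | 0.24 |
| 20% | 0.79 | 0.28 |
| 30% | 0.84 | 0.32 |
| 50% | 0.94 | 0.42 |

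None of these figures allows for dropout or for clustering within clinicians or centres.

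**The case against.** Four objections have weight.

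- **The target is a starting point.** The text says that 164 is an initial aim and a minimum. The Randomization section prepares 100 numbers for each of four centres, and the limitations allow for more centres. A reader might infer that enrolment is fixed at 164, but the document does not say so. What stands is that no rule takes the trial to 209, and extra centres are mentioned only as an answer to dropout.
- **The origin of 209 is inferred.** The match is exact and does not depend on the number of covariates, but other inputs also give 209. One example is a joint test of 8 predictors at f² = 0.075. This stands, so the authors should supply the inputs.
- **209 may be a proper interaction calculation.** A reader might infer from the match that 209 is merely the main comparison made two-sided. That does not follow. The interaction of arm with one moderator is a single coefficient, and this is a standard way to size it. At 209 such an interaction of 0.39 SD per SD would have 80% power.
- **Low power is not a fixed fact.** The figures depend on assumed interaction sizes and on how much variance the model explains. If it explains 20–50%, power at 164 for the larger interaction is 79–94%. This stands, and no single power range for modest interactions should be written into the protocol.

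It is also fair that the central research question is the main effect, and that the Study context section already describes the work on empathy as an exploration. The abstract carries no such qualification.

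**Conclusion.** The concern holds in a limited form. The certain part needs no assumption: the initial target is 45 patients below the size that the protocol says its interaction regression needs, no rule closes the gap, and the abstract promises a moderation answer without qualification.

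The rest depends on reading 209 as a two-sided, single-coefficient calculation at d = 0.39. On that reading, with little other variance explained, power at 164 is about 70%. It is about 24% for an interaction half as large (28–42% if the model explains 20–50% of WAI variance). A joint test of the BLRI and SEE would need about 257, so 209 would also fall short for that.

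The documents do not show that 209 is wrong, or that the authors intend to read a non-significant interaction as absence of moderation. This point does not affect the analysis of the main comparison.

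**What to change.** Keep 164 as the target for the main comparison, and change the text around it:

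1. State the effect size, the sidedness and the number of tested terms behind 209.
2. State that at 164 the interaction analyses fall short of the protocol's own required size. If the authors confirm that 209 was a two-sided, single-coefficient calculation at d = 0.39, add that power is then about 70%.
3. Label moderation as exploratory in the analysis section, report each interaction with its 95% confidence interval, and say that a non-significant interaction will not be taken as evidence of no moderation.
4. Amend the Results sentence of the abstract so that it promises an answer on the main effect and an exploratory estimate of the role of empathy.

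The cost is wording only, with no added patients or procedures. The downside is that the moderation claim becomes less favourable.

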## Introduction

Due to cultural differences between patients with a migrant background (hereafter: migrant patients) and clinicians, mental health care faces many challenges. Such differences cause higher thresholds for help-seeking and incongruencies in diagnosis and treatment, which do not meet these patients’ needs (1). Challenges stem from language barriers, diverse idioms of distress, and distinct explanatory models between migrant patients and predominantly non-migrant mental health providers (2). Idioms or expressions of distress provide alternate means of conveying emotional upset and are indicative of personal and cultural contexts. In mental health care, migrant patients experience higher dropout rates, longer care trajectories, lower treatment effectiveness, and more frequent involuntarily admissions to clinical care (3, 4). Despite the positive fact that migrant patients’ access to mental health care appears to have improved, they often do not receive the necessary care (5). This could result from a limited view of these patients experiencing mental health symptoms and inadequate focus on their social context, cultural roots, environment, and cultural identity, which fails to recognize and comprehend the individual behind the patient (6, 7). Despite the consideration of migrant patients’ cultural identities in diagnostic procedures to gain better insights into their symptoms, these patients continue to receive inadequate diagnoses and often feel misunderstood (1, 6, 7).

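### The figure of 164 is both the minimum for 80% power and the initial enrolment aim, so at the inputs that reproduce it any missing session-five WAI-12 takes power below 80%

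*Protocol article*

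**What the plan says.** The Sample size section gives the result of the calculation as a minimum: "The power analysis indicated that at least 164 patients would need to be included in this study". The calculation is "for the comparison of two independent groups (t-test"), "with a power of (1-ß) = .80", "a significance level <.05" and equal allocation. The target difference is described as half an SD and given the value .39. Sidedness is not stated. A larger figure, 209, is given for the regression with interaction terms. The section then closes on enrolment: "Initially, the investigators aim to enroll 164 patients".

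The SD comes from work on the WAI-12, which is the patient version. Under Data collection and in Table 1, patients complete it once, within one week of the fifth treatment session.

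Strengths and limitations acknowledges that "participants are free to stop participating and may drop out for many reasons", says that this may compromise power, and mentions extra centres as a possible response. No loss rate is given there, and the Sample size section does not mention loss. Under Data analysis, missing data are to be multiply imputed if assumptions allow, within an intention-to-treat analysis.

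**The concern.** A two-sample t-test calculation returns the number of patients whose outcome enters the comparison. The article uses that number as the enrolment aim. The two coincide only if every enrolled patient reaches session five and completes the WAI-12. A patient who leaves earlier has no observed WAI.

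At stake is the reading of the result. If power is quoted as 80% but the number analysed supports less, a null finding will be given more weight than the design justifies. This matters here because the Study context section links an approach to health insurers to significant results.

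**Working it through.** **Inputs.** From the Sample size section: total N = 164, power .80, alpha .05, ratio 1:1, and a difference of half an SD written as .39. Not stated there: sidedness, and whether .39 is a raw difference or the standardised effect d. Taken literally, .39 is half of an SD of .39 / .5 = .78, so d = .39 / .78 = .50. Alternatively, .39 was entered directly as d. That gives four readings.

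**Reproducing 164.** By the normal approximation, n per arm = 2(z_alpha + z_power)² / d². For d = .39, one-sided: 2(1.645 + 0.842)² / .39² = 12.37 / .1521 = 81.3, so 82 per arm and 164 in total. The noncentral t calculation that G*Power uses also gives 164, with power .800. By the same noncentral t method the four readings need:

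| d | Sides | Total N for 80% power |
|---|---|---|
| .39 | one | 164 |
| .39 | two | 210 |
| .50 | one | 102 |
| .50 | two | 128 |

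Only the first matches the article.

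**Power of 164 enrolled under loss.** The number analysed is 164 × (1 − loss): 164 × .9 = 147.6 (148), 164 × .8 = 131.2 (131) and 164 × .7 = 114.8 (115). The loss rates are assumed. Noncentral t, alpha .05, equal arms, no information recovered by imputation:

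| d, sides | No loss (164) | 10% (148) | 20% (131) | 30% (115) |
|---|---|---|---|---|
| .39, one | 80.0% | 76.3% | 71.7% | 66.8% |
| .39, two | 69.9% | 65.4% | 60.1% | 54.5% |
| .50, two | 88.9% | 85.6% | 81.1% | 75.7% |
| .50, one | 93.9% | 91.7% | 88.5% | 84.6% |

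**Slack in 164.** For d = .39 one-sided there is none, since 164 is the smallest even total that reaches 80%. For d = .50 two-sided, the tolerable loss is 1 − 128/164 = 22%.

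**Enrolment that would keep 164 evaluable**, as N / (1 − loss): 164/.9 = 183, 164/.8 = 205 and 164/.7 = 235, rounded up.

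**The case against.** The strongest objection is that the shortfall is conditional. Read literally, half an SD means d = .50. Two-sided, that needs 128 evaluable patients, so 164 enrolled already covers about 22% loss. This stands, and it means one cannot say outright that the trial lacks 80% power. It does not rescue the text, because d = .50 does not yield a requirement of 164. The article states that "at least 164 patients would need to be included in this study to obtain results" of practical relevance, and on the inputs behind that statement there is no margin.

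Second, the article discloses the risk, since Strengths and limitations says that power may be compromised. True, but this is not quantified and does not reach the Sample size section, where 80% stands alone.

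Third, a reader might infer that substantial drop-out is expected in this trial, because the Introduction says that "migrant patients experience higher dropout rates". That sentence concerns mental health care in general. For this trial the article says only that participants may drop out. The size of any loss by session five is unknown.

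Fourth, a reader might infer that 164 is a cap. It is worded as an initial aim, and the Randomization section prepares four lists of 100, or 400 allocations, so enrolment could go further without new lists. But the only larger figure, 209, is given for the regression and not as a loss allowance.

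Fifth, imputation may recover something. There is no earlier WAI, but there is a session-one BLRI, and a clinician WAI-36 may exist for a patient who reached session five and did not complete the questionnaire. How much these recover has not been calculated, and the WAI-36 cannot help for patients who leave earlier. The power table makes no allowance for it.

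Rules for replacing patients or for deciding when to add centres may be left to the full protocol, so their absence is not part of this point.

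**Conclusion.** The point holds in conditional form. The same number serves as the minimum for 80% power and as the initial enrolment aim, with no allowance for a missing session-five WAI-12, while the article itself names drop-out as a threat to power.

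The consequence depends on inputs that the article leaves unclear. With d = .39 one-sided, the only reading that reproduces 164, each 10 percentage points of loss costs roughly 4 to 5 points of power. With d = .39 two-sided, 80% is missed even with complete data. With d = .50 the aim has slack, up to about 22% loss two-sided and beyond 30% one-sided. The article supports neither the conclusion that power is certainly below 80% nor the conclusion that it is safely above it. All figures rest on assumed loss rates, equal loss in the two arms and a simple t-test on observed outcomes.

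**What to change.** In the Sample size section:

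1. State the standardised effect and the sidedness entered in G*Power, and reconcile .39 with half an SD.
2. Say that 164 refers to patients with a completed patient WAI-12. If reconciliation shows that a different evaluable number is required (128 for d = .50 two-sided, 210 for d = .39 two-sided), give that number instead.
3. Replace the single 80% with the power that 164 enrolled patients deliver at stated loss rates, for example 10%, 20% and 30%, labelled as assumptions.

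This is a change of wording and needs no additional patients. Its cost is a less favourable stated power if .39 is the standardised effect. It does not restore 80% on that reading. Should the sponsor want that, the enrolment figures at the end of the working show what it would take for the one-sided calculation.
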